**Fig. 3 Fig3:**
[figure not shown]
Hierarchical test procedure used for the primary endpoint analysis

#### Other analyses

All secondary analyses will be performed in the intention-to-treat population (all randomized patients) and also in the per protocol population (patients with no major deviation of the protocol) at a bilateral 5 % alpha risk.

Unless otherwise specified, categorical variables will be compared by a chi-squared test or Fisher test as appropriate. Continuous variables will be compared by a Student's *t* test or Wilcoxon test as appropriate (when two groups are compared) and by an analysis of variance (ANOVA) or Kruskal-Wallis test as appropriate (when more than two groups are compared).

##### Adjusting the analysis of the primary endpoint for potential confounders

The primary endpoint analysis will be adjusted on the stratification factors (centers and underlying chronic respiratory disease) and on potential confounders using a multivariate analysis (linear regression model). Potential confounders will be: a prior chronic respiratory disease; a PaO_2_/FiO_2_ < 200 mmHg; a prior psychiatric disease.

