### Randomization

Eligible consecutive patients are randomly allocated to one of the three study arms. Randomization and concealment are achieved using a centralized, secure, computer-generated, interactive, web-response system accessible from each study center (CleanWEB, Telemedicine technologies S.A.S, Boulogne-Billancourt, France) [21]. The randomization is balanced by blocks of variable and undisclosed size and stratified on the center and the presence of a chronic respiratory insufficiency. Before randomization, the presence of the inclusion criteria and the absence of the non-inclusion criteria are verified and entered in the electronic case report form. In each ICU, patients are enrolled by the local physicians and a clinical research nurse and/or clinical research assistant. The randomization day is the study day 1.

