### At day 1 (baseline)

Demographic data and medical history, including the current clinical history with the reason for ICU admission, Simplified Acute Physiology Score III severity score [26], and Sequential Organ Failure Assessment score [27], are collected.

Treatments including NIV (and its settings), fluid therapy, catecholamine infusion, and endotracheal intubation are recorded. Laboratory tests include serum (and urine if diuresis is present) electrolyte levels determination, serum glucose level, urea and creatinine concentration, and arterial blood gas determination. Respiratory and hemodynamic parameters before the beginning of the NIV session (respiratory rate, exhaled tidal volume, PaO_2_/FiO_2_ ratio, heart rate, arterial pressure) are collected.

The research team administers to the patient, or to a proxy if the patient is not able to answer, the baseline Hospital Anxiety and Depression Scale (HADS) questionnaire [28] and Short Form-36 (SF-36) [29] in order to determine the baseline health-related quality of life.

### At each NIV session, until NIV discontinuation or day 28

The prescribed duration of the NIV session is recorded. Prior to each NIV session, immediately after NIV is correctly set (5 minutes), at 30 minutes, and at 1, 2, 3, 4, 6, 8, 12, 16, 20, 24 hours depending on the length of each NIV session, and at the end of the session, the following data are collected:Respiratory comfort assessed by a blinded evaluator (nurse from another unit) with the use of a numeric visual scale [14]The same respiratory and hemodynamic parameters as the initial onesAgitation assessed by Richmond Agitation-Sedation Scale [30].

For each NIV session, the need for physical contention or sedative or anxiolytic treatments is assessed and recorded. The tolerance of sensory isolation is recorded, as well as attempts to pull off the NIV mask or headphones. At the end of each session, data for its exact duration, the reason of its premature ending if appropriate, and the need for endotracheal intubation are collected. Furthermore, arterial blood gases are reported when these tests are performed as clinically indicated. The occurrence of nasal bridge ulcers or irritations is also recorded. For the “musical intervention” group, the type of music chosen and the feeling experienced during the session are recorded.

### At NIV discontinuation, ICU discharge, or day 28

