#### Primary endpoint

The change in respiratory comfort at initiation and after 30 minutes of the first NIV session will be analyzed in the intention-to-treat population. For each patient, the variation in respiratory comfort will be calculated by the difference between the measurement at “30 minutes” and "before." This change will then be compared between the treatment groups, based on a Student’s *t* test. If the test application conditions are not met, a Wilcoxon test will be applied.

Because three parallel groups are included in the study, three comparisons are possible: "musical intervention" and "NIV only" (comparison 1), "sensory deprivation" and "NIV only" (comparison 2), and "musical intervention" and "sensory deprivation" (comparison 3). These comparisons will be performed in a pre-established hierarchical test procedure (see Fig. 3), in order to maintain the alpha risk of 5 % in a strong sense:Step 1: We will perform comparisons 1 and 2, both at 2.5 % (bilateral) alpha risk.Step 2: In the event of non-significance of the two previous tests, we will stop the test procedure and conclude the negativity of the trial; in the case of statistical significance of both previous tests, we will perform comparison 3 at 5 % (bilateral) alpha risk; in the case of statistical significance of only one of the two previous tests, we will perform comparison 3 at 2.5 % (bilateral) alpha risk.Step 3: If comparison 3 was performed at 2.5 % alpha risk and is significant, the non-significant comparison performed in step 1 may be performed again at an alpha risk of 5 % (Fig. 3).

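### The supportive adjusted model for the primary endpoint leaves out pre-NIV comfort, and its respiratory term should be reconciled with the randomisation stratum

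*Protocol article*

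**What the plan says.** The confirmatory analysis (protocol article, *Statistical analysis, Primary endpoint*) works on a change score. "For each patient, the variation in respiratory comfort will be calculated by the difference between the measurement at" 30 minutes and the one before NIV. Arms are compared with an unadjusted Student's t test, or a Wilcoxon test if its conditions fail, inside the hierarchical procedure.

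A second analysis of the same endpoint appears under *Other analyses*. It is to be "adjusted on the stratification factors (centers and underlying chronic respiratory disease) and on potential confounders using a multivariate analysis (linear regression model". The list is then fixed: "Potential confounders will be: a prior chronic respiratory disease", followed by PaO2/FiO2 below 200 mmHg and prior psychiatric disease.

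Three other places bear on this:

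- *Randomization*: allocation is "stratified on the center and the presence of a chronic respiratory insufficiency".
- *Data collection and follow-up*: comfort is recorded "Prior to each NIV session, immediately after NIV is correctly set (5 minutes), at 30 minutes" and later. Among the day-1 measurements, "respiratory rate, exhaled tidal volume, PaO_2_/FiO_2_ ratio, heart rate, arterial pressure) are collected".
- *Evolution of respiratory comfort during NIV sessions*: the linear mixed model takes its stable covariates from the confounder list above and adds centre as a fixed effect.

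**The concern.** In a regression of a change score, the baseline value of the same scale is usually the most informative covariate available. It is collected here, yet the list that begins "Potential confounders will be: a prior chronic respiratory disease" has no place for it. The adjusted estimate will then carry a wider confidence interval than the data allow.

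The respiratory term is also unclear. Randomisation uses chronic respiratory *insufficiency*. The adjusted model says it uses the stratification factors but calls this one chronic respiratory *disease*, then repeats it among the confounders. An analyst cannot tell whether this is one variable written twice or two variables with different definitions. PaO2/FiO2, collected as a ratio, enters only as above or below a cut.

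**Working it through.** **1. The plan's own sample size.** Inputs from *Sample size calculation*: difference 2, SD 2.5, power 80 %, two-sided alpha 5 % and then 2.5 %. With the two-sample t test (noncentral t) and standardised difference 2/2.5 = 0.8:

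- alpha 5 %: 25.5, so 26 per arm, as stated;
- alpha 2.5 %: 30.99, so 31 per arm (93 in total), as stated;
- 5 % loss: 31/0.95 = 32.6, so 33 per arm (99 in total), as stated.

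The planned size is correct for the unadjusted test and is not in question.

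**2. Adding pre-NIV comfort.** Let s0 and s1 be the within-arm SDs before NIV and at 30 minutes, and rho their correlation. With other covariates in the model, read these as the values after those covariates.

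- Change-score variance: s0² + s1² − 2·rho·s0·s1.
- Residual variance with baseline as covariate: s1²(1 − rho²).
- Difference: s0² − 2·rho·s0·s1 + rho²·s1² = (s0 − rho·s1)², which is never negative.

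With s0 = s1 = s these become 2s²(1 − rho) and s²(1 − rho²), so the ratio is (1 + rho)/2. It does not depend on s, so it does not matter that the article leaves open whether 2.5 is the SD of a change or of a single score.

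| rho (assumed) | variance ratio | reduction in variance | standard error ratio |
|---|---|---|---|
| 0.3 | 0.65 | 35 % | 0.806 |
| 0.5 | 0.75 | 25 % | 0.866 |
| 0.7 | 0.85 | 15 % | 0.922 |

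The treatment contrast is unchanged. Regressing the change, or the 30-minute score, on group and baseline gives the same group coefficient; only the baseline slope shifts, by 1. The cost is one residual degree of freedom.

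**3. The double listing.** In a simulated data set of 93 patients, the model with intercept, two group terms, two centre terms, respiratory disease, PaO2/FiO2 below 200 and psychiatric disease has rank 8. Adding the respiratory column again leaves the rank at 8, and the treatment estimate (−1.187) and its standard error (0.629) do not move. An identical duplicate costs no precision. If the two were coded differently, one degree of freedom would be spent.

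**4. PaO2/FiO2 cut at 200.** Assume a normal covariate, a cut at its median and a linear relation to the outcome. None of these is in the article. A median split then keeps 2/pi = 0.637 of the explained variance. The residual variance of the continuous form relative to the split is (1 − r²)/(1 − 0.637r²): 0.985, 0.965 and 0.935 at assumed correlations r of 0.2, 0.3 and 0.4. The gain is 1.5 % to 6.5 % of variance, well below that from baseline comfort.

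**The case against.** The strongest reply is that this model is not the primary analysis. It stands under *Other analyses* and drives neither the hierarchical procedure nor the sample size. That is right, and it sets the limit of the point. At a change SD of 2.5, 31 per arm, alpha 2.5 % and rho 0.5, a baseline-adjusted test would have about 91 % power against 80 % unadjusted. A reader might infer that the trial is giving up that power. The documents do not support this as a consequence of the adjusted section, because the confirmatory test is the unadjusted t test and rewording the supportive model leaves it as it is. Nor is baseline ignored altogether: it enters through the change score.

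A reader might also infer that the model adjusts for the wrong stratum. The article does not establish that. It defines neither *insufficiency* nor *disease*, and the sentence itself presents the respiratory term as the stratification factor: "adjusted on the stratification factors (centers and underlying chronic respiratory disease". One variable, loosely worded, is a fair reading. The second listing even has a use, since the confounder list is the route by which the respiratory factor reaches the mixed model. What stands is that the two sections use different terms for something fixed at randomisation.

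Finally, a reader might extend the baseline argument to the mixed model. *Secondary endpoints* lists the measurement before initiation among the repeated comfort scores, so there the pre-session score is already a response. Entering it again as a covariate would put it on both sides of the model.

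**Conclusion.** The point holds as a free improvement to a supportive analysis. Omitting pre-NIV comfort leaves the residual variance of the adjusted primary-endpoint model higher than it need be. Adding it lowers that variance by 35 %, 25 % or 15 % at rho 0.3, 0.5 or 0.7, equivalent to standard errors about 19 %, 13 % or 8 % smaller. These figures assume equal variance at both times and a rho that the documents do not give. The direction needs neither assumption, apart from the one degree of freedom.

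The respiratory wording is a reconciliation matter with no demonstrated loss of precision. The PaO2/FiO2 cut is a minor choice, and its continuous form brings a linearity assumption of its own. None of this touches the confirmatory test, its power or the planned 99 patients.

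**What to change.** In the section on adjusting the primary endpoint:

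- add the comfort score before the first NIV session as a covariate;
- enter centre and the respiratory stratum as recorded by the randomisation system, once each, and use one term for that stratum here and under *Randomization*;
- keep prior psychiatric disease;
- optionally enter PaO2/FiO2 as a continuous term, with a check of linearity.

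In the mixed model for comfort, name the respiratory stratum explicitly so that it is not lost when the duplicate is removed from the confounder list. Do not add baseline comfort there as a covariate where the pre-session score is already one of the repeated responses.

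The cost is the wording of one model and one cross-reference. No new data, patients or procedures are needed. The change should be made before the data are analysed by arm.

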##### Primary endpoint analysis in the per protocol population

The change in respiratory comfort at initiation and after 30 minutes of the first NIV session between the groups will also be compared in the per protocol population defined previously (this comparison does not constitute the primary analysis of the study).

##### Evolution of respiratory comfort during NIV sessions

The number of measures of respiratory comfort for each patient will be variable, since the duration and number of NIV sessions is at the discretion of the physician. The data structure is complex and has three levels:Level 1: respiratory discomfort measuresLevel 2: patientsLevel 3: centers.

For this type of (repeated) data, it is essential to take into account correlations between measurements from the same patient. A linear mixed effects model (including fixed and random effects) will be used to model the effect of the three interventions on the evolution of respiratory comfort during NIV sessions. This model will include:Fixed effects○ The variable "time"○ The randomization group (categorical variable with three different levels) and its interaction with time○ Stable characteristics over time (see potential confounders described above)○ Characteristics which vary over time: the number of NIV sessionsRandom effects ("subject effect").

The need for a model with random intercept and slope (versus random intercept only) will be assessed at the time of the analysis with a likelihood ratio test. An appropriate modeling of time will be performed if its effect is not linear.

Correlations between patients from the same center could also be taken into account by the inclusion of a "random center effect" (level 3). However, such a mixed model may be unsuitable in practice because of the limited number of clusters (only three participating centers). In this setting, it is preferable to include a fixed center effect [33], and this is the solution that will be implemented in this analysis.

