##### Evolution of respiratory and hemodynamic parameters during NIV sessions

This analysis will be conducted according to the same principles as for the analysis of the evolution of respiratory comfort.

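### The mixed models that pool NIV sessions omit the session as a level, so within-session correlation is unmodelled and the arm-by-time standard error may be too large or too small

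*Protocol article*

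**What the plan says.** In the protocol article, the section on evolution of respiratory comfort during NIV sessions says that "The data structure is complex and has three levels" and lists them: "Level 1: respiratory discomfort measuresLevel 2: patientsLevel 3: centers". It explains that the number of ratings per patient will vary "since the duration and number of NIV sessions is at the discretion of the physician", and that "it is essential to take into account correlations between measurements from the same patient". The random part is a subject effect. On the slope it adds: "The need for a model with random intercept and slope (versus random intercept only) will be assessed at the time of the analysis", by a likelihood ratio test. Center enters as a fixed effect. The number of NIV sessions enters as a fixed covariate, listed among the characteristics that change over time.

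The data collection section, under the heading for each NIV session, sets the measurement grid: before the session, at 5 and 30 minutes, then at fixed hours up to 24 h, "depending on the length of each NIV session, and at the end of the session, the following data are collected". This continues until NIV discontinuation or day 28. The secondary endpoints repeat the grid for every later session.

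For respiratory and hemodynamic parameters the article says: "This analysis will be conducted according to the same principles" as for comfort. Secondary analyses are tested "at a bilateral 5 % alpha risk".

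**The concern.** The measurement grid has up to 14 points in a session (before, 5 min, 30 min, ten hourly marks, end), and a patient may have many sessions. The nesting is therefore measure within session within patient within center. Ratings from one session share that session's mask fit, ventilator settings and clinical state. The stated model treats them as independent given the patient. The plan's own reason for modelling same-patient correlation applies equally to same-session correlation.

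Nothing else in the stated model fills the gap. A fixed covariate for the number of sessions shifts the mean and leaves the correlation as it was. The likelihood ratio test chooses between random effects at patient level only. The provision for non-linear time concerns the mean curve.

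At stake is the validity or the precision of the arm-by-time comparison in every model that pools sessions.

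**Working it through.** **The plan's own figures.** The article gives none for the mixed model. Its sample size reproduces and does not depend on this point. With a standardised difference of 2/2.5 = 0.8, a two-sample t test needs 25.5, so 26 per arm, at 5 %, and 30.99, so 31 per arm, at 2.5 %. Then 31/0.95 = 32.6, so 33 per arm and 99 in total.

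**Inputs.** From the document: 33 per arm, SD 2.5 (variance 6.25) and the repeated grid. Assumed, because the document does not give them: the number of sessions and all variance components.

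**Why the direction depends on time.** Take S sessions of M ratings, session-intercept variance v_s and residual variance v_e. A model with a patient intercept only puts session variance into its residual, which becomes about v_e + v_s·M(S−1)/(SM−1). The true variance of the time slope is proportional to
- v_e, if time runs within the session (the session intercept cancels);
- v_e + M·v_s, if time runs almost wholly between sessions.

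With patient variance 2.0, v_s = 1.5, v_e = 6.25 − 2.0 − 1.5 = 2.75, M = 5 and S = 4, the model's residual is 2.75 + 1.5 × 15/19 = 3.93.
- Within session: √(3.93/2.75) = 1.20, so the standard error is too large.
- Across sessions: √(3.93/10.25) = 0.62, so it is too small.

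**Simulation, set B.** No true arm effect, 33 per arm, 300 trials per setting, 4 or 8 sessions of 5 ratings, and the variances above unless shown. Entries are model SE divided by true SE, then type I error at a nominal 5 %.

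| Setting | Patient intercept only | Slope chosen by likelihood ratio | With session effects |
|---|---|---|---|
| No session variance | 0.96-0.99; 5-6 % | 0.96-0.99; 5-6 % | 0.99-1.02; 5 % |
| Time within session, v_s 1.5 | 1.25; 1.3 % | 1.25; 1.3 % | 1.08; 3.3 % |
| Same, session-slope variance 0.3 | 1.08; 4.0 % | 1.08; 4.0 % | 1.08; 4.3 % |
| Same, session-slope variance 0.75 | 0.85-0.92; 8-10 % | 0.94-0.98; 7-8 % | 0.96-1.03; 6 % |
| Time across sessions, v_s 0.75-1.5 | 0.62-0.74; 14-23 % | 0.92-0.96; 7-8 % | 1.01-1.05; 5-6 % |

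Monte Carlo error is about 4 % on the ratio and √(0.05 × 0.95/300) = 1.3 points on a 5 % rate. The hand calculation agrees within that error.

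**Simulation, set A.** 99 patients, about 5 sessions, 3-5 ratings each, about 300 trials per setting. SDs were 1.5 (patient), 1.2 (session) and 1.0 (residual); slopes were per hour within a session.
- Session intercepts only, patient-intercept model: empirical SD 0.131, model SE 0.143, type I error 3.7 %. A model with the session level has SE 0.102. The precision loss is 0.131/0.102 = 1.28, or 28 %.
- Session slopes added (SD 0.6 and 1.0), patient-intercept model: type I error 8.1 % and 14.8 %.
- Patient slope included: type I error 6.3 % and 7.0 %.

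**The case against.** The strongest reply is that the document gives no session variance, session count or intraclass correlation, so no misstatement can be demonstrated from it. With no session variance the planned model performs properly, and with a session-slope variance of 0.3 the two errors nearly cancel. This stands. A reader might infer that the standard errors are certainly wrong, or wrong in a known direction, and the document supports neither.

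Second, the plan already allows a patient random slope. The rates of 8-23 % belong to the intercept-only model and should not be read as the plan's expected error rate. With the patient slope, 6.3 % and 7.0 % lie 1.0 and 1.6 Monte Carlo standard errors above 5 %, so neither is clearly inflated alone. The remaining excess is modest.

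Third, a reader might quote a 40 % wider interval from 0.143/0.102. That sets a model-reported standard error against the standard error of a different estimator. On the empirical SD the loss is 28 %, and a wide interval is an inefficient one, not a false conclusion.

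Fourth, one might infer that the model adjusts for each patient's total number of sessions, a consequence of tolerance after randomization. The article lists the covariate among characteristics that vary over time. A total does not vary, so a running count is the natural reading.

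Deferral to a fuller analysis plan helps little. The article does not leave the structure open: it fixes the levels, the random effects, the slope rule and the handling of center.

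**Conclusion.** The omission is plain in the text: the session is a level of the data and not of the model. It affects the models that pool sessions, namely comfort over subsequent sessions and the respiratory and hemodynamic parameters. The consequence is conditional on sessions differing within a patient. The arm-by-time standard error may then be too large or too small, according to how time is defined and to the session intercept and slope variances.

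Under the assumed variances, type I error ran from about 1 % to 23 % with a patient intercept only. It was about 6-8 % with the patient slope where the intercept-only model was anti-conservative, and about 3-6 % with session effects. These figures illustrate the risk and are not estimates for this trial.

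The reach is limited. The primary endpoint is one change per patient in the first session. In any first-session-only analysis, session and patient coincide and no level is missing. The change should be made, since it is nearly free, but it does not threaten the trial's main conclusion.

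**What to change.** For the models that pool sessions:
- State the session as a level between measures and patients, giving four levels, with center kept as a fixed effect.
- Add a random intercept for session nested in patient beside the subject effect, and a session-level slope in time under the same likelihood-ratio rule.
- Define time as time since the start of that session.
- State that the time-varying number of NIV sessions is the session's rank (first, second and so on).
- Apply the same to the respiratory and hemodynamic parameters.

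The cost is an added session random effect in the model code and a few sentences of text. Measurements are already collected session by session, so no new data are needed.
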